
**Fig. 1 Fig1:**
[figure not shown]
Timeline of PAROS Study

### Outcomes

The primary outcome is to determine whether low-pressure (7 mm Hg) instead of standard-pressure (12 mm Hg) pneumoperitoneum during laparoscopic colonic resection leads to a reduction of the length of hospital stay of at least 1 day. The theoretical discharge date is the date of medical discharge of the patient, evaluated daily between 7 and 8 a.m., in accordance with predefined criteria, which are no pain requiring the use of analgesics more than stage 2, no nausea or vomiting, no fever of more than 38 °C, resumption of a normal diet, transit (passage of flatus/stool), patient mobilization, and patient acceptance. The real discharge date is the date of discharge including a possible continuation of hospitalization for non-medical reasons (i.e., waiting for convalescent home, personal suitability of the patient).

Secondary outcomes are to determine how low-pressure pneumoperitoneum (7 mm Hg) influences: patient's post-operative pain (visual analogue scale after 2, 4, 8, and 24 h after surgery), the consumption of level 1, 2, and 3 analgesics, the transit and gas recovery time (days), the time before first time sitting and walking, the evolution of the perioperative cardiovascular and respiratory parameters (arterial blood pressure, heart rate, cardiac output, vascular filling, driving pressure, arterial oxygen saturation [SAO_2_], and post-exercise circulatory occlusion [PECO]), the operating time (from incision to closing, in minutes), the amount of bleeding, the visual quality of the procedure, the laparoscopy conversion rate to normal pressure or laparotomy, ability to achievean R0 resection in cancer surgery, the number of lymph nodes on the specimen and the rate of medical and surgical complications during the first postoperative 30 days (according to the DINDO classification). It seemed important to us to select post-operative pain because it is one of the major factors influencing the patient’s length of stay and very interesting to know whether a lower insufflation pressure makes it possible to reduce pain related to abdominal distention on the one hand and scapular pain on the other hand, which is described as extremely frequent in most laparoscopic procedures. The amount of analgesics (level 1, 2 and 3) is an objective data wich allows us to evaluate pain, wich is a subjective data. In addition, regarding the number of deaths currently associated with chronic opioid use, it seemed that defining whether low pressure allows opioid savings in the post-operative period was a major objective. We also know that taking opioids increases the time before transit resumes and that this influences the length of stay.

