## Objectives

The primary objective is to determine whether low-pressure (7 mm Hg) instead of standard-pressure (12 mm Hg) pneumoperitoneum for patients undergoing laparoscopic colonic resection results in a reduced length of hospital stay of at least 1 day. The secondary objectives are the comparison between groups of post-operative pain, analgesics consumption, 30-day post-operative morbidity, operative time, bleeding, quality of visibility during intervention, conversion rate, perioperative cardiovascular and respiratory function, time to passage of flatus and stool, time to sitting out and mobilizing, and quality of oncological resection (lymph node dissection and curative resection).

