### Consent and randomization

During the pre-inclusion visit, the investigator will inform the participant and answer all questions regarding the purpose, nature of, foreseeable risks, and the expected benefits of the clinical trial. The investigator is responsible for obtaining informed consent from the participant. An original copy of the information note and signed consent will be given to the patient. The other original copy will be retained by the investigator as part of the study documents in an area inaccessible to third parties. After the written consent of the patient is obtained, randomization will take place the day before or the day of the procedure but at the latest before the incision. When an investigator (“operator” surgeon) wishes to perform the randomization/inclusion after verifying the eligibility of the participant, they will send a randomization application document to the statistician of the study, who will send back a patient number (of three digits corresponding to the inclusion rank), an anonymous letter code (four letters), and the result of the randomization arm, namely group A (experimental): insufflation at low pressure (5–7 mm Hg) or group B (control): insufflation at standard pressure (12–15 mm Hg). The two groups will be balanced with a ratio of 1:1. Randomization will be performed by using the following method: for each subject entering the study, a number K between 0 and 9 will be drawn randomly from Excel. The subject will be assigned to the control group if K is 0 or even or to the “low pressure” group if K is odd. Simple randomization does not necessarily lead to homogenous groups. However, a deviation of less than 20% should have little effect on power loss, and the groups should equilibrate with larger sample sizes (more than 50).

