### Intervention

The “operator” surgeon is the surgeon who performs the procedure. The team is made up of six different surgeons, each with their own patients and using the same surgical techniques. The “evaluator” surgeon is the surgeon who validates the patient’s discharge according to predefined and objective criteria. The operating surgeon does not validate the discharge of his own patients. The patient also ignores the arm in which he or she was randomly assigned. The results of randomization are known only by the department’s clinical researchers and kept in a password-protected Excel database. The result is communicated only to the “operator” surgeon on the day of the operation. He knows the randomization arm because it is up to him to adjust the insufflation pressure during the procedure. On day 0, the “operator” surgeon performs a laparoscopic colectomy by using the AirSeal® medical device (ConMed, Utica, NY, USA) and adjusts the insufflation pressure in accordance with the results of the randomization: low-pressure insufflation at 7 mm Hg or standard-pressure insufflation at 12 mm Hg. Different anesthesia and analgesia may affect the secondary outcomes, post-operative pain scores, consumption of analgesics, and recovery time. This is why the anesthetic and analgesic protocol are standardized in both groups and explained in schematic form in the Appendix. The intra-operative protocol starts before the introduction of the trocar: we infiltrate the orifices with 2% naropeine. Then the patient receives a continuous infusion of ultiva, ketamine (0.3 mg/kg as a loading dose and then 0.15 mg/kg per hour until the end of the surgery), and xylocaine (continuous dose of 1.0 mg/kg, stopped 1 h before the end of the surgery). One hour before the end of the surgery, we perform a morphine bolus of 0.1 mg/kg, 50 mg of profenid, and 1000 mg of paracetamol. In the post-operative care room, a morphine titration will be performed if necessary (the amount of morphine given is notified) and the patient receives 1000 mg of paracetamol again 1 h after the surgery is completed. In the post-operative period, the patient systematically receives 1000 mg of paracetamol every 6 h and 50 mg of profenid every 6 h for 48 h. The patient also receives 50 mg of topalgic only if needed and all doses are notified (maximum 8 per 24 h). Perioperative respiratory and cardiovascular management are also standardized. Cardiovascular data will include systolic blood pressure, diastolic blood pressure, mean arterial pressure, heart rate, cardiac index, stroke volume, and stroke volume variation. We also collect the volume of hydration and filling, balance of inputs and outputs, and total doses of ephedrine and noradrenaline (if needed). Respiratory data will include tidal volume, end-tidal CO_2_, respiratory frequency, peak pressure, peak pressure, plateau pressure, driving pressure, compliance (exhalation pressure at 0 and 8 mm Hg), exhalation volume (at 0 and 8 mm Hg), inspired fraction of O_2_, O_2_ saturation, and functional residual capacity. The aerosols are used only if necessary in case of obstructive pathology (asthma or chronic obstructive pulmonary disease). The aerosol used if necessary is Salbutamol (beta-2 mimetics). The degree of muscle relaxation is monitored throughout the interventions using the TOF (Train of Four): four short stimulations of 0.2-ms duration, spread over 2 s. It measures the ratio between the response of the fourth and first stimulation (T4/T1 ratio) or counts the number of responses (from 0 to 4). We measure the TOF via the response of the ulnar nerve (thumb adduction) by using a device located on each patient’s wrist. For all procedures, the TOF must be equal to 0. The post-operative mobilization of the patient and the gastrointestinal recovery will be carried out in accordance with the ERAS (Enhanced Recovery After Surgery) early rehabilitation protocol [15]. Criteria for discharge will be carried out by a surgeon different from the one who performed the operation (“evaluator surgeon”). The patient will be hospitalized for the post-operative period in the colorectal unit of Magellan Medico-Surgical Centre. The follow-up will be standardized regardless of the randomization arm. All inpatient and outpatient adverse events will be recorded and reported. As part of the standard care in our colorectal unit, all patients have a post-operative consultation at 30 days (+15 days maximum) Fig. 1.

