### Sample size

The calculation of the number of subjects required is based on the primary endpoint, which is a decrease in hospital length of stay of at least 1 day in patients operated on laparoscopically for malignant or benign colonic pathology using a low-pressure pneumoperitoneum with the medical insufflation device AirSeal®. The activity of the Colorectal Unit of the Magellan Medico-Surgical Centre was 170 colonic laparoscopic resections in 2017, and the average hospital stay of patients in this control arm would be 5 ± 2 days based on available data. As such, in unilateral formulation, to show a difference (1 day) with an alpha risk of 5% and a power of 90%, there should be 69 patients recruited per group, resulting in a total of 138 patients.

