### Statistical analysis

The main analysis will focus on all randomly assigned patients (intention-to-treat analysis). The alpha risk is 5% and the power is 90%. Given the main variables studied, there will be no missing data for analysis of the primary outcome. The descriptive statistical analysis will include the following for each quantitative parameter at each time: average, standard deviation, minimum, maximum, median and quartiles, and number of missing values. The categorical variables will be expressed by the frequency of distribution and the associated 95% bilateral confidence intervals. For the primary endpoint, which is theoretical length of hospital stay, the two groups will be compared by using Student’s *t* test if, as suggested by a preliminary study, the distribution of the variable does not deviate significantly from a Gaussian distribution; otherwise, a Mann–Whitney test will be used. For the secondary endpoints, the categorical criteria will be analyzed by using a chi-squared test. In the event that the chi-squared validity criteria are not verified, an exact probability test will be used. Quantitative secondary criteria will be compared by *t* test or Mann–Whitney according to their distribution in the sample considered. All tests will be bilateral at risk of the first species set at 5%. The analysis will be performed by using IBM SPSS Statistics, version 20 software (IBM, Armonk, NY, USA).

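### Conversion to normal pressure can occur only in the low-pressure arm, so a between-arm test of the pooled conversion rate cannot be read as a difference in conversion risk

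*Protocol article*

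**What the plan says.** The Outcomes section of the protocol article includes, in its list of secondary outcomes, "the laparoscopy conversion rate to normal pressure or laparotomy". It is worded as a single rate. Nothing in the article separates its two parts, limits the pressure part to one arm, or defines a matching event for controls.

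The Objectives section makes the secondary outcomes comparative: "The secondary objectives are the comparison between groups of post-operative pain" opens a list that goes on to "operative time, bleeding, quality of visibility during intervention, conversion rate". Conversion appears there undivided.

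Under Statistical analysis, for the secondary endpoints, "the categorical criteria will be analyzed by using a chi-squared test". An exact test is the fallback where the validity conditions of the chi-squared test fail, and all tests are two-sided at 5%.

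The Intervention section gives the two assignments as "low-pressure insufflation at 7 mm Hg or standard-pressure insufflation at 12 mm Hg". The Consent and randomization section describes the control assignment as a range: "group B (control): insufflation at standard pressure (12–15 mm Hg". The sections differ on the exact figures and should be reconciled, but under either one a control patient is at standard pressure from the start.

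**The concern.** A patient already at normal pressure cannot be converted to it. One of the two ways of meeting the endpoint is therefore closed to the control arm. Every low-pressure case raised to normal pressure adds an event to one side of the comparison only, and always in the same direction.

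The two parts also answer different questions. How often low pressure has to be abandoned is a question of feasibility and adherence. Whether low pressure leads to more open operations is a question about a clinical consequence that both arms can suffer. If the two are pooled and tested, a significant excess in the low-pressure arm may be reported although laparotomy is equally frequent in both arms, and a reader of the pooled rate alone could not tell.

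**Working it through.** **The plan's own figure.** The article gives no event rate or power for conversion, so there is nothing to reproduce for this endpoint. The group size used below is the article's 69 per arm. It reproduces from the Sample size inputs: difference 1 day, SD 2 days, one-sided 5%, power 90% give 69 per group (calculated power 90.2%).

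**Inputs from the article.** 69 patients per arm; two-sided 5%; chi-squared test with an exact fallback. The fallback was applied as Fisher's test when an expected count is below 5, which is one reading of the validity conditions.

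**Assumptions.** L = true laparotomy rate, the same in both arms, 5% or 10%. Q = share of low-pressure patients raised to normal pressure, 5%, 10% or 15%. The article states neither.

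**Pooled rate by arm.**
- Control: L, because Q is zero there by design.
- Low pressure, events independent (one patient may have both): L + (1 − L) × Q.
- Low pressure, events in different patients: L + Q.

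Example with L = 5%, Q = 10%: independent, 0.05 + 0.95 × 0.10 = 14.5%; different patients, 0.05 + 0.10 = 15%. Control: 5%.

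**Probability of a significant result.** All pairs of event counts from 0 to 69 in each arm were enumerated, and the binomial probabilities of the pairs with p < 0.05 were summed.

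| L (both arms) | Q (low pressure only) | Pooled low vs control, independent | Significant | Pooled low vs control, different patients | Significant |
|---|---|---|---|---|---|
| 5% | 0% | 5.0% vs 5% | 2.1% | 5% vs 5% | 2.1% |
| 5% | 5% | 9.8% vs 5% | 16.4% | 10% vs 5% | 17.8% |
| 5% | 10% | 14.5% vs 5% | 47.5% | 15% vs 5% | 50.8% |
| 5% | 15% | 19.3% vs 5% | 75.7% | 20% vs 5% | 79.1% |
| 10% | 0% | 10.0% vs 10% | 4.9% | 10% vs 10% | 4.9% |
| 10% | 5% | 14.5% vs 10% | 12.3% | 15% vs 10% | 14.0% |
| 10% | 10% | 19.0% vs 10% | 32.1% | 20% vs 10% | 37.6% |
| 10% | 15% | 23.5% vs 10% | 57.5% | 25% vs 10% | 65.4% |

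The rows with Q = 0% are also the result for laparotomy alone: the test stays within its nominal 5% when both arms can have the event. With Q between 5% and 15%, the probability runs from 12.3% to 79.1%, while the true laparotomy rates are identical in every row.

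**If two rates are meant.** The pressure component tested alone compares Q with 0%. At Q = 10% the same enumeration gives a significant result in about 70% of trials. That tells the reader only that some low-pressure cases were raised, which the low-pressure proportion already shows.

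**The case against.** The strongest counter-argument is that the pooling is inferred. The phrase sits in a long list, the article never says that the two events will be combined, and the sentence on chi-squared tests is generic. The author may intend one rate for each type of conversion, and a condensed article may leave the tabulation to the full protocol. This reading is possible. Under it the laparotomy comparison is sound, but the stated between-group comparison of the pressure part would still be made against a structural zero. The wording needs changing on either reading.

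A second argument is that having to abandon low pressure is a real consequence of being assigned to it. The chi-squared test is then a valid test of whether the proportions, as defined, differ. This stands. A reader might infer from the table that the test itself is biased or that its results are false positives. The documents do not support that: the fault lies in reading the pooled difference as a difference in conversion risk.

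A reader might also infer that the trial's main safety or feasibility comparison is compromised. The article does not rank conversion that way. It lists bleeding, operating time, visual quality, completeness of resection, lymph nodes and 30-day complications as well, and the outcomes it singles out for explanation are pain and analgesic use.

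Finally, the control range of 12–15 mm Hg might seem to give controls an equivalent event. A rise within that range is still standard pressure, so it is not a conversion to it. It does mean that controls could exceed an assigned value of 12 mm Hg, which matters for how any symmetric event is defined.

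**Conclusion.** The point holds as a defect in a secondary endpoint. As worded, one component can occur only in the low-pressure arm, so the pooled difference cannot be interpreted as a difference in conversion risk, and a between-arm test of the pressure component alone adds nothing.

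The size depends on rates that the protocol does not give. With equal laparotomy rates of 5% or 10% and 5% to 15% of low-pressure cases raised, the pooled comparison is significant in about 12% to 79% of trials. The low end comes from a 10% laparotomy rate with 5% raised. The high end comes from a 5% laparotomy rate with 15% raised in different patients. If few cases are raised, the practical effect is small. The primary endpoint, the sample size and the primary analysis are not touched.

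**What to change.** Report the two components separately.

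1. **Conversion to laparotomy:** make this the between-arm comparison, by chi-squared or exact test as already planned, with a 95% confidence interval for the risk difference.
2. **Conversion from low to normal pressure:** report as a proportion with a 95% confidence interval in the low-pressure arm only, as a measure of feasibility and adherence beside the intention-to-treat result, without a between-arm test.
3. **If a comparison of pressure changes is wanted:** define an event that both arms can have, such as any increase above the assigned pressure, and record it in both arms. This first requires the assigned pressures in the Consent and randomization and the Intervention sections to be reconciled.

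The cost is one changed definition for a secondary outcome, plus confirmation that the case report form records each type of conversion. The Data management section does not name either type among the intra-operative data, so their capture should be checked rather than assumed.

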### Withdrawal from the study

The participant who wishes to abandon or withdraw consent to participate will no longer be followed in the context of the protocol but will receive medical and surgical follow-up as standard for all post-operative colectomy patients in our unit. Abandonment is a decision of an included participant to assert the right to interrupt participation in a research, at any time during the follow-up, without incurring any prejudice or having to justify the decision. A withdrawal of consent is a decision of a participant to reconsider the decision to participate in this research and to assert the right to cancel informed consent at any time during the follow-up and without incurring any prejudice and without having to justify him- or herself.

### Duration of the trial

Based on 170 colonic laparoscopic resections performed in our unit in 2017, the recruitment of 138 patients in this trial will be performed over 1 year. The duration of participation of each participant will be 2 months, and the total duration of the trial will be 14 months. The inclusion started in January 2019 and was scheduled to finish in January 2020.

### Sample size

The calculation of the number of subjects required is based on the primary endpoint, which is a decrease in hospital length of stay of at least 1 day in patients operated on laparoscopically for malignant or benign colonic pathology using a low-pressure pneumoperitoneum with the medical insufflation device AirSeal®. The activity of the Colorectal Unit of the Magellan Medico-Surgical Centre was 170 colonic laparoscopic resections in 2017, and the average hospital stay of patients in this control arm would be 5 ± 2 days based on available data. As such, in unilateral formulation, to show a difference (1 day) with an alpha risk of 5% and a power of 90%, there should be 69 patients recruited per group, resulting in a total of 138 patients.

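### The 138-patient sample size is computed one-sided but every test is declared two-sided, so the planned analysis has about 83% power, not the stated 90%

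*Protocol article*

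**What the plan says.** **Protocol article, Sample size.** The calculation rests on the primary endpoint, described as "a decrease in hospital length of stay of at least 1 day". The planning values come from the unit's own activity: "the average hospital stay of patients in this control arm would be 5 ± 2 days based on available data". The error rates and direction are set "in unilateral formulation, to show a difference (1 day) with an alpha risk of 5% and a power of 90" percent, and the result is 69 patients per group, 138 in all.

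**Protocol article, Statistical analysis.** Near the start of the section: "The alpha risk is 5% and the power is 90" percent. The primary endpoint, theoretical length of stay, is compared by Student's t test, or by Mann–Whitney if the distribution departs from Gaussian. After the tests for the primary and secondary endpoints have been described, the section closes the topic with "All tests will be bilateral at risk of the first species set at 5" percent. Nothing there or elsewhere in the article exempts the primary comparison.

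**The concern.** A one-sided 5% test puts its critical value at 1.645 standard errors. A two-sided 5% test puts it at 1.960. A sample size that gives 90% power against the lower threshold must give less against the higher one. The article takes the sample size from the first rule and the analysis from the second, and claims the power of the first for both.

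Two things are at stake. First, the stated type II error for the primary endpoint is wrong for the analysis that is declared, and readers will attach the 90% to the two-sided test because both appear in the same section. Second, the article holds two incompatible success criteria. A result in favour of low pressure with a two-sided p-value between 0.05 and 0.10 succeeds under the Sample size section and fails under the Statistical analysis section. If this is not settled before the data are seen, the criterion could be chosen afterwards. Moving to the one-sided rule would double the false-positive rate in the favourable direction, from 2.5% to 5%.

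**Working it through.** **Inputs**

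- Difference d = 1 day, α = 5%, power 90%, one-sided, 69 per group: Sample size section.
- Standard deviation: the ± 2 days in the same section, read as an SD and taken as equal in both arms (an assumption; the article does not label it).
- Allocation 1:1: Consent and randomization section.
- No allowance for loss: the Statistical analysis section expects no missing primary data.
- Test direction in the analysis, two-sided 5%: Statistical analysis section.

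**Step 1: reproduce the plan's figure.** For two means with equal groups,

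n per group = 2 (z_α + z_β)² SD² / d².

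One-sided 5%, 90% power: 2 × (1.645 + 1.282)² × 4 / 1 = 68.5, rounded up to **69**. The article's figure is reproduced exactly.

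**Step 2: rule out a two-sided origin.**

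- Two-sided 5%, 90% power: 2 × (1.960 + 1.282)² × 4 = 84.1, so **85** per group.
- Two-sided 5%, 80% power: **63** per group.

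Neither gives 69, so the number itself confirms that the calculation was one-sided.

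**Step 3: power of the declared test at 69 per group.** The standardised signal is

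d / (SD √(2/n)) = 1 / (2 √(2/69)) = 2.937.

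| Test at 5% | Normal approximation | Noncentral t, 136 df |
|---|---|---|
| One-sided | Φ(2.937 − 1.645) = 90.2% | 89.9% |
| Two-sided | Φ(2.937 − 1.960) = **83.6%** | **83.0%** |

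The type II error under the declared test is 100 − 83.0 = 17.0% (16.4% by the normal approximation), against the stated 10%.

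**Step 4: what 90% power would take under the two-sided test.**

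- Patients: 85 per group (170 in total) by the formula the article evidently used. By noncentral t, 85 per group gives 89.99%, so strictly 86 (172 in total). That is 32 to 34 more than planned.
- Detectable difference at 69 per group: (1.960 + 1.282) × 2 × √(2/69) = 1.10 days by the normal approximation, and 1.11 days by noncentral t.

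**Step 5: sensitivity (illustrative).**

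- If the Mann–Whitney fallback is used on near-Gaussian data, with an assumed relative efficiency of 0.955, two-sided power is about 81%.
- If three patients per arm had no primary outcome (an assumption that the article does not make), 66 per arm would give 81.4%.

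**The case against.** The strongest reply is that the primary test was meant to be one-sided. The objective is directional throughout, the Sample size section chose a one-sided formulation openly, and the sentence on two-sided testing comes directly after the secondary endpoints, so it may have been written with those in mind. On that reading 90% power stands. But the sentence covers all tests, the primary comparison is described in the same section, and no exception is made. If a one-sided primary test was intended, the Statistical analysis section is wrong and still has to be corrected. What stands is that the 83% figure follows from taking that section as governing.

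A second reply is that little harm follows. The two-sided test protects the type I error, the estimate is unaffected, and 83% power is commonly acceptable. That is true and is a reason not to demand more patients. It does not rescue the claim of 90%, since a gap of about 7 points is not rounding, and it does not settle which criterion decides the primary result.

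A third reply is that a full protocol or analysis plan may resolve the matter. The point is not an omission, however: the article prints both conflicting statements.

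**Conclusion.** The concern holds. The sample size is one-sided and the declared analysis is two-sided, and the 90% power belongs only to the former. With 69 per group, a true difference of 1 day and an SD of 2 days in both arms, the declared two-sided 5% t test has about 83% power (83.0% by noncentral t, 83.6% by normal approximation), some 6 to 7 points below the claim. The size of the shortfall depends on reading ± 2 as a common SD and on use of the t test. The contradiction depends on neither. Because it concerns the direction of the primary test, it must be resolved before the data are seen.

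**What to change.** Keep the two-sided 5% test and the 138 patients, and correct the power statement in both sections.

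- **Sample size:** replace the one-sided justification with wording such as: *With 138 patients (69 per group), a two-sided 5% t test has 83% power to detect a difference of 1 day in mean length of stay, assuming a standard deviation of 2 days in both groups, and 90% power to detect 1.11 days.*
- **Statistical analysis:** replace the bare 90% with the same 83% for 1 day, and leave the two-sided rule as it stands.

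The cost is two sentences and a less favourable stated power. Recruitment and conduct do not change.

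Two other routes would also remove the contradiction, at a higher price. Raising the total to 170–172 would keep 90% power with the two-sided test and is the route to take if 90% is a firm requirement. Declaring the primary test one-sided at 5% would keep 90% at the present size, but it accepts a 5% rather than 2.5% false-positive rate in the favourable direction and would have to be fixed and dated before any outcome data are examined.
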